# The impact of maintaining serum potassium ≥3.6 mEq/L vs ≥4.5 mEq/L on the incidence of new-onset atrial fibrillation in the first 120 hours after isolated elective coronary artery bypass grafting – study protocol for a randomised feasibility trial for the proposed Tight K randomized non-inferiority trial

**DOI:** 10.1186/s13063-017-2349-x

**Published:** 2017-12-28

**Keywords:** Potassium, Coronary Artery Bypass Grafting, Atrial Fibrillation, Cardiac Surgery

## Abstract

**Background:**

Atrial fibrillation (AF) occurs in approximately one in three patients after cardiac surgery, and is associated with increased short-term and long-term mortality, intensive care unit (ICU) and hospital stay, and increased cost of care. In an attempt to reduce AF incidence in these patients, serum potassium (K+) levels are commonly maintained at the high end of normal (4.5–5.5 mEq/L). However, such potassium supplementation is without proven benefit, and is not without negative consequences. It carries clinical risk, negatively impacts patient experience and is both time-consuming and costly. This protocol describes a randomised controlled pilot trial to assess the feasibility of a proposed randomised non-inferiority trial to investigate the impact of maintaining serum potassium ≥ 3.6 mEq/L vs ≥ 4.5 mEq/L on the incidence of new-onset atrial fibrillation in the first 120 hours after isolated elective coronary artery bypass grafting.

**Methods:**

Design: this is a randomized feasibility trial as a pilot for a randomized non-inferiority trial. Participants: are 160 patients undergoing isolated coronary artery bypass grafting at two centres. Allocation: patients will be randomized (1:1) to protocols aiming to maintain serum potassium at either ≥ 3.6 mEq/L (“relaxed control”) or ≥ 4.5 mEq/L (“tight control”). Primary analytic aim: was to assess the feasibility and acceptability of planning and delivering the intervention and trial methods to inform a full-scale non-inferiority trial. Outcome: the primary indicative efficacy outcome measures being field-tested are feasibility of participant recruitment and randomization, maintaining a protocol violation rate < 10%, and retaining 90% patient follow up 28 days after surgery. The primary clinical outcome measure of the future full “Tight K Study” will be incidence of AF after cardiac surgery.

**Discussion:**

The Tight K Pilot will assess the feasibility of conducting the full trial, which is intended to confirm or refute the efficacy of current potassium management in preventing AF after cardiac surgery.

**Trial registration:**

ClinicalTrials.gov, NCT03195647. Registered on 23 May 2017. Last updated 19June 2017.

**Electronic supplementary material:**

The online version of this article (doi:10.1186/s13063-017-2349-x) contains supplementary material, which is available to authorized users.

## Background

Approximately one in three patients is affected by atrial fibrillation (AF) after cardiac surgery, with most episodes occurring in the first five postoperative days [1–3]. AF occurrence is associated with increased short-term and long-term mortality [3–6], intensive care unit (ICU) and hospital stay [7, 8], and cost of care [9]. Persistence of this association after adjustment for potential confounding factors suggests that it may be causal [10]. The incidence and associated costs of AF are expected to increase as the surgical population ages [11].

Potassium plays an important role in cardiac electrophysiology [12]. Serum concentrations ([K^+^]) are commonly low following cardiac surgery [13], and appear marginally lower in in non-surgical cohorts among those suffering atrial arrhythmias [14]. Despite an absence of proof that this association is causal, efforts to maintain serum [K^+^] in the “high-normal” range (4.5–5.5 mEq/L), as opposed to just intervening if potassium drops below its lower “normal” threshold, are considered “routine practice” for AF prevention in patients post-surgery in many centres across the world [15].

The efficacy of the practice of maintaining high-normal serum potassium levels remains unproven and data supporting it are extremely limited, being derived from observational rather than interventional studies [15]. Indeed, there are no data to demonstrate that maintaining a high-normal potassium level is beneficial in these circumstances, or that aggressive replenishment of potassium in these patients improves outcome [16]. Meanwhile, potassium supplementation may cause discomfort or harm. Routine central venous potassium administration in the early post-operative period, when oral supplementation is not possible, is time-consuming, costly, and associated with clinical risk: rapid infusion can prove fatal [17], and leaving central venous catheters *in situ* for the sole purpose of potassium replacement increases infection risk. The annual costs of intravenous potassium exceed those for other drugs in many cardiothoracic units due to the large quantities administered [18]. Nursing time (e.g. for drug checks and administration) will also add to this cost. Oral potassium supplementation is commonly associated with gastrointestinal side effects and is often poorly tolerated by patients [19].

We here describe a trial (Tight K Pilot) designed to assess the feasibility of performing a randomized controlled non-inferiority trial to assess any impact of targeted maintenance of serum K+ concentration ≥ 3.6 mEq/L vs ≥ 4.5 mEq/L on AF incidence after coronary artery bypass grafting (CABG).

## Methods/design

The trial is a randomised feasibility trial. This protocol was written following the Standard Protocol Items: Recommendations for Interventional trials (SPIRIT) checklist (see Additional file 1).

Hypothesis for the pilot trial: it will be feasible to recruit and randomise 160 patients over a period of 6 months, maintain < 10% protocol violation rate, and retain 90% of patients for follow up 28 days post-surgery. The protocol violation rates are defined subsequently (“Endpoints of the Trial”).

Hypothesis for the main trial: AF will be no more common (based on a non-inferiority margin of 10%, see following) after cardiac surgery when serum potassium levels are maintained at ≥3.6 mEq/L (“relaxed control”) than when they are maintained at ≥4.5 mEq/L (“tight control”).

### Setting

The Tight K Pilot will be conducted in two UK centres – the Barts Heart Centre, Barts Health National Health Service (NHS) Trust and St George’s University Hospitals NHS Trust, both in London, UK.

### Trial population

Eligible patients are those undergoing elective CABG surgery.

### Exclusion criteria

Age < 18 yearsPrevious AFConcurrent patient involvement in another clinical trial assessing post-operative interventionsOngoing infection/sepsis at the time of surgeryPre-operative high-degree atrio-ventricular (AV) blockPre-operative serum potassium (K^+^) > 5.5 mEq/LCurrent or previous use of medication for the purposes of cardiac rhythm managementDialysis-dependent end-stage renal failureUnable to give informed consent

### Informed consent procedure

Eligible participants will be given a copy of the patient information sheet (PIS) at a pre-operative hospital appointment or upon admission prior to surgery, at which time a delegated member of the research team will be available to discuss the trial further and to answer any questions that the patient may have. Research staff may approach patients prior to their scheduled hospital appointment via post, telephone or email to discuss the study.

All participants will be given at least 24 hours to consider whether or not to take part in the trial. If willing to take part, they can consent at any time prior to surgery. Written consent will be obtained on a consent form.

### Randomisation

One hundred and sixty eligible participants with informed written consent will be allocated in a 1:1 ratio using an online database (https://sealedenvelope.com/) to receive either tight (K^+^ ≥4.5mMol/L) or relaxed (K^+^ ≥3.6mMol/l) potassium control. Patients will be randomised on the day of surgery. The allocation will be stratified by site.

### Trial treatment period

A flowchart of the trial treatment intervention process is shown in Fig. 1. The trial treatment intervention period will commence when the patient is admitted to ICU or any other post-operative care facility after surgery, according to local practice. It will end 120 hours (5 days) after that time point, or with occurrence of a clinically identified episode of AF (see following) - whichever occurs first.

**Fig. 1 Fig1:**
[figure not shown]
Flowchart of the study protocol. CABG, coronary artery bypass grafting; AF atrial fibrillation; post-op, post-operative

### Tight potassium control

Patients randomised to the tight-control group will receive potassium supplementation if their serum K^+^ falls below 4.5 mEq/L (current practice).

### Relaxed potassium control

Those randomised to the relaxed-control group will receive potassium supplementation only if their serum K^+^ level drops below or equals 3.6 mEq/L.

### Potassium supplementation

The administration route used for all potassium replacement will be prescribed according to clinician preference and given according to existing standardised protocols. This supplementation may include intravenous (iv) or oral potassium formulation, administration of potassium-rich nasogastric feeding regimens or recommending the consumption of potassium-rich foods.

### Routine clinical practice

All other clinical practice (including the use of magnesium supplementation, the use of beta-blockers or anti-arrhythmic agents, the route of potassium administration, and blood tests) will be routine, and independent of trial allocation. In particular, the frequency with which serum [K^+^] is monitored will be according to existing protocols and clinician/nursing staff preference (Fig. 1).

### Patients with AF

In keeping with recognised international criteria, atrial fibrillation will be defined as an episode of AF lasting ≥ 30 seconds that is clinically detected and/or electrocardiographically confirmed (on either a 12-lead electrocardiogram (ECG) or telemetry) [20]. Routine clinical monitoring will be supplemented by continuous Holter monitoring (eMotion Faros 180, Technomed Ltd) for the first 120 postoperative hours in all participants. Once a patient has a clinically identified period of AF, the trial treatment period ends and then there will be no restriction on potassium supplementation and they should be treated according to current practice (Fig. 1). The schedule of trial enrolment, interventions and assessments is shown in Fig. 2 (SPIRIT figure).

**Fig. 2 Fig2:**
[figure not shown]
Standard Protocol Items: Recommendation for Interventional Trials (SPIRIT) figure depicting the schedule of enrolment, interventions and assessment. EQ-5D-5L, 5-level Euroqol-5D questionnaire

### Endpoints of the trial

The primary outcome measure of this pilot trial is the performance on feasibility endpoints.

Primary questions for the pilot trial are to investigate:Whether it is feasible to recruit 160 patients over a period of 6 months (20% of those eligible)Whether it is possible to randomise patients into groups for potassium replacement if K+ <4.5 mEq/L (usual practice) vs. < 3.6 mEq/L (lower limit of the normal range)Whether it is feasible for the protocol violation rate to be no more than 10% (see following)Whether it is feasible to maintain follow-up rates > 90% at 28 days after CABG

Reasons for a protocol violation may include:A patient from the relaxed-control group being treated as if they are in the tight-control group or a patient from the tight-control group being treated as if they are in the relaxed-control groupFailure of randomisationAlteration in planned surgeryFailure of the Holter monitoring processLack of data completion

Secondary endpoints for the pilot trial: in order to further inform the proposed main randomised controlled trial endpoints, the following additional outcomes will be collected:Incidence and total duration of new-onset AF arrhythmia post-surgery until day 5. This is the primary endpoint for the future full Tight K Trial.Mean critical care duration of stay.Mean hospital duration of stay.Incidence and total duration of all other arrhythmias until day 5 (120 hours), defined using standard diagnostic criteria.Incidence of in-patient mortality.Incidence of 28-day mortality.Cost-effectiveness.

Holter recordings will be analysed after day 5 by clinical staff blinded to group allocation. The time of all clinically identiifed episodes of AF will be documented and contemporaneous Holter monitoring recordings will be reviewed to confirm or deny the AF diagnosis after day 5 by clinical staff blinded to treatment allocation. Cardiac arrhythmias that were not detected clinically will also be documented. A copy of all Holter reports will be sent to the patient’s primary admitting surgical team.

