For each 24-hour study period (1 through 5), recorded serum potassium concentrations and potassium administration (dose and route) will be documented. Medication at hospital discharge will be collated, including whether anticoagulation is commenced for atrial fibrillation. Duration of stay on ICU, total hospital stay and mortality will be recorded. Adverse events attributed to K^+^ replacement, including gastrointestinal symptoms from oral K^+^ replacement will be collated. Detailed information will be collected on the resource use associated with delivering each protocol, including the total number of potassium replacement interventions.

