### Statistical analysis

#### Power and sample size

One hundred and sixty patients are to be recruited from two centres, and randomly allocated in a ratio of 1:1. As this is a pilot trial to assess feasibility, power calculations are not appropriate. If the anticipated recruitment, follow-up and retention rates are demonstrated over a 6-month recruitment period, this would confirm the feasibility of a multicentre randomised controlled non-inferiority trial in 1682 patients with an estimated eligible cohort of 8700 patients over 3.5 years.

The sample size calculation for the main trial is based on a baseline incidence of AF of 35% [1, 21]; a clinically relevant non-inferiority margin of 10%; a true difference in favour of tight potassium control of 2%, 90% power; a one-sided alpha of 2.5% (equivalent to a two-sided alpha of 5%) and < 10% protocol violations. Due to this anticipated protocol violation rate, a greater number of patients will be recruited to the full study, as not all will be included in the final analysis.

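### The pilot checks that staff follow the allocated potassium trigger, but no endpoint asks whether following it separates the arms in serum potassium or potassium given

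*Protocol article*

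**What the plan says.** The main-trial hypothesis (Methods/design) compares AF when serum potassium is kept at or above 3.6 mEq/L with AF when it is kept at or above 4.5 mEq/L. The arms are delivered as two replacement triggers (Tight potassium control; Relaxed potassium control).

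Endpoints of the trial lists four primary questions: recruiting 160 patients in 6 months; "Whether it is possible to randomise patients into groups for potassium replacement if K+ <4.5 mEq/L (usual practice) vs. < 3.6 mEq/L"; a violation rate of at most 10%; and "Whether it is feasible to maintain follow-up rates > 90% at 28 days after CABG". The first violation listed is treating a patient as if in the other arm. The secondary list covers AF, other arrhythmias, length of stay, mortality and cost-effectiveness. Achieved potassium is in neither list.

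Outcome analyses defines the primary outcome as numbers recruited and randomised, protocol fidelity and follow-up. Power and sample size then says: "If the anticipated recruitment, follow-up and retention rates are demonstrated over a 6-month recruitment period, this would confirm the feasibility" of a 1682-patient non-inferiority trial.

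The relevant data will exist. Data collection says: "For each 24-hour study period (1 through 5), recorded serum potassium concentrations and potassium administration (dose and route) will be documented". It also counts relaxed-arm patients wrongly given potassium, tight-arm patients from whom it was wrongly withheld, and replacement interventions overall.

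**The concern.** Adherence and separation are different quantities. The two arms call for different action only when a measured value lies between the two triggers. If relaxed-arm patients seldom drop below 4.5 mEq/L without help, or if few samples are taken, every patient can be managed as allocated while the potassium distributions differ little.

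Two features of the pragmatic design make the size of the contrast uncertain. On testing, "the frequency with which serum [K^+^] is monitored will be according to existing protocols and clinician/nursing staff preference". On what is given, "This supplementation may include intravenous (iv) or oral potassium formulation, administration of potassium-rich nasogastric feeding regimens or recommending the consumption of potassium-rich foods", so interventions of very different strength all count as supplementation.

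Lost contrast usually makes a superiority trial fail. In a non-inferiority trial it makes success more likely. A pilot is well placed to show whether the two policies deliver a contrast, yet this one could meet its stated criteria without that being asked.

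**Working it through.** **1. Reproduce the plan's main-trial size.** Inputs from Power and sample size: AF 35% under tight control, true difference 2 points (so 37% under relaxed control), margin 10 points, one-sided alpha 2.5%, power 90%, allowance for 10% violations.

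n per arm = (1.960 + 1.282)² × (0.35×0.65 + 0.37×0.63) / (0.10 − 0.02)² = 10.507 × (0.2275 + 0.2331) / 0.0064 = 756.2, rounded up to 757. The total is 1514, and 1514/0.9 = 1682.2. The stated 1682 reproduces.

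**2. Chance of declaring non-inferiority at a delivered AF difference d.**
P = Φ((0.10 − d)/SE − 1.96), with SE = √[(0.35×0.65 + (0.35+d)(0.65−d))/757].

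- d = 0: SE 0.02452; Φ(4.079 − 1.96) = 98.3%
- d = 0.02 (design): SE 0.02467; Φ(3.243 − 1.96) = 90.0%
- d = 0.06: SE 0.02490; Φ(1.606 − 1.96) = 36%
- d = 0.12: SE 0.02509; Φ(−0.797 − 1.96) = 0.3%

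**3. Effect of diluted contrast.** Two assumptions, neither in the article: a fully separated relaxed policy raises AF by 10, 12 or 15 points, and the delivered effect shrinks in proportion to the separation achieved.

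| Separation achieved | 10 points | 12 points | 15 points |
|---|---|---|---|
| 100% | 2.5% | 0.3% | about 0% |
| 75% | 16.9% | 5.9% | 0.7% |
| 50% | 52.1% | 36.2% | 16.9% |
| 25% | 85.9% | 80.8% | 71.3% |
| 0% | 98.3% | 98.3% | 98.3% |

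**4. How often the arms would call for different action.** Assume untreated potassium is normal with SD 0.4 mEq/L. The share of readings between 3.6 and 4.5 is then:

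- mean 4.0: Φ(1.25) − Φ(−1.00) = 74%
- mean 4.3: Φ(0.50) − Φ(−1.75) = 65%
- mean 4.6: Φ(−0.25) − Φ(−2.50) = 40%
- mean 4.8: Φ(−0.75) − Φ(−3.00) = 23%

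These are shares of readings, not of patients. Even at mean 4.8, one independent reading a day for five days would put 1 − 0.775⁵ = 72% of patients in the band at least once. Correlation between readings would lower that figure. The article does not say which mean applies.

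**The case against.** A reader might infer that nothing in the primary criteria bears on treatment contrast, or that the potassium records go unused. The article supports neither. Crossover in either direction counts towards the 10% limit, protocol fidelity by arm is part of the primary outcome, and wrongly given or withheld potassium can hardly be identified without the readings. Leakage through dietary advice to a relaxed-arm patient above the trigger would also count as inappropriate supplementation. Follow-up data are to be tabulated by arm and used to refine the main design. What is missing is narrower: a named outcome for separation among patients treated as allocated.

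A reader might also expect the two arms to end with nearly identical potassium. The article gives no support for that. Its Background says potassium is commonly low after cardiac surgery, which fits the lower means in step 4, where most readings fall between the triggers. Near-complete overlap is not excluded by the criteria, but it is not forecast by anything in the text.

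The strongest objection is that this is a pragmatic comparison of two triggers, with 3.6 a floor. A relaxed-arm patient at 4.6 satisfies the policy, and if most patients behave that way, similar AF rates are a valid answer about the policy. This stands far enough to rule out a hard stop at an arbitrary potassium difference. It does not remove the need to know the contrast: the Discussion intends to conclude whether supplementing to a high target is effective or has no benefit, and a trial with little contrast could not support that.

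Finally, the confirming sentence does not launch a trial by itself, and the pilot hypothesis does include the violation limit. But that sentence names neither violations nor separation. By-arm process tables may well be left to a fuller document. The endpoint lists and the confirming sentence are set out here.

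**Conclusion.** The point holds in a limited form. Adherence to the triggers is a primary criterion; the separation that adherence produces is not an endpoint of any kind, and confirmation of the 1682-patient trial is not conditioned on it.

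The direction of the harm is firm: if the relaxed policy truly increases AF, less contrast means a greater chance of declaring non-inferiority. Its size is not. The rise from 0.3% to 36% for an assumed 12-point excess at half contrast, or from 2.5% to 52% for 10 points, rests on assumed effects and proportional dilution. The 98.3% at zero contrast rests only on the plan's own 35% AF rate, margin and analysed number.

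This should be fixed, but it is not critical, because the data are collected and crossover is already counted.

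**What to change.** In Endpoints of the trial, add between-arm separation as a named feasibility outcome. Report by arm and 24-hour period, up to the end of trial treatment:

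- mean serum potassium, with the between-arm difference and 95% CI;
- the proportion of patients with at least one reading between the two triggers;
- the proportion given potassium.

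In Power and sample size, amend the confirming sentence so that it also requires the violation limit to be met and the Trial Steering Committee to review separation against an expectation recorded before any results by arm are seen. This review informs the decision; it need not be an automatic stop.

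No new data are needed and neither sample size changes. The cost is one more table and one more criterion on which the pilot may be judged.

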#### Health-related quality of life

All participants will complete a quality of life questionnaire (5-level Euroqol-5D (EQ-5D-5 L)) prior to their surgery and also at 28-day follow up, by telephone or post.

#### Post-operative follow up at 28 days

Patients surviving to hospital discharge will be followed up by telephone or post 28 days after randomization, to determine mortality and further episodes of heart rhythm problems (if known).

### Data collection

The data collected will be utilized to fulfill two distinct purposes:To assess whether the primary and secondary endpoints of this study are met.To assess the efficiency of data completion to ensure protocol compliance. To do this, the same variables that we intend to collate in the full future study will be collected in this pilot study.

The following will be collated over the trial study period (6 months):Total number of patients undergoing isolated CABGNumber of patients screened, invited to participate, and recruited into the study.Patients not followed up at 28 daysNumber of protocol cross-overs and detailsPatients in the relaxed-control group who inappropriately received potassium supplementationPatients in the tight-control group who inappropriately did not receive potassium supplementation

For each protocol violation, a root-cause analysis will be undertaken that will examine staff roles, timing, education, and other preventable factors. All patients will also have a full medical history taken and various clinical examinations as part of usual care. The following will be recorded:Patient initialsEthnic originCardiac medication and indication (including beta-blockers, calcium channel blockers, ACE-inhibitors, angiotensin receptor blockers (ARBs), aldosterone receptor antagonists, anticoagulation)Medical history: chronic obstructive pulmonary disease (COPD)/lung disease, diabetes mellitus (and type), hypertension, myocardial infarction (MI), chronic kidney disease (CKD), transient ischaemic attack (TIA) or stroke/cerebrovascular accident (CVA), and family history of arrhythmia (and details)Imaging data: left ventricular ejection fraction (LVEF)/left atrial (LA) size, mitral regurgitation or stenosis (defined as moderate or worse)HAS-BLED and CHADSVASC scores will be calculated for patients at baseline

For each 24-hour study period (1 through 5), recorded serum potassium concentrations and potassium administration (dose and route) will be documented. Medication at hospital discharge will be collated, including whether anticoagulation is commenced for atrial fibrillation. Duration of stay on ICU, total hospital stay and mortality will be recorded. Adverse events attributed to K^+^ replacement, including gastrointestinal symptoms from oral K^+^ replacement will be collated. Detailed information will be collected on the resource use associated with delivering each protocol, including the total number of potassium replacement interventions.

